## Abstract

**Background:**

The birth of a child with a cleft lip, whether or not in association with a cleft palate, is a traumatic event for parents. This prospective, multidisciplinary and multi-centre study aims to explore the perceptions and feelings of parents in the year following the birth of their child, and to analyse parent–child relationships. Four inclusion centres have been selected, differing as to the date of the first surgical intervention, between birth and six months. The aim is to compare results, also distinguishing the subgroups of parents who were given the diagnosis *in utero* and those who were not.

**Methods/Design:**

The main hypothesis is that the longer the time-lapse before the first surgical

intervention, the more likely are the psychological perceptions of the parents to affect the harmonious development of their child. Parents and children are seen twice, when the child is 4 months (T0) and when the child is one year old (T1). At these two times, the psychological state of the child and his/her relational abilities are assessed by a specially trained professional, and self-administered questionnaires measuring factors liable to affect child–parent relationships are issued to the parents. The Alarme Détresse BéBé score for the child and the Parenting Stress Index score for the parents, measured when the child reaches one year, will be used as the main criteria to compare children with early surgery to children with late surgery, and those where the diagnosis was obtained prior to birth with those receiving it at birth.

**Discussion:**

The mental and psychological dimensions relating to the abnormality and its correction will be analysed for the parents (the importance of prenatal diagnosis, relational development with the child, self-image, quality of life) and also, for the first time, for the child (distress, withdrawal). In an ethical perspective, the different time lapses until surgery in the different protocols and their effects will be analysed, so as to serve as a reference for improving the quality of information during the waiting period, and the quality of support provided for parents and children by the healthcare team before the first surgical intervention.

**Trial Registration:**

ClinicalTrials.gov Identifier: NCT00993993.

## Background

### The malformation and its consequences

Cleft lip with or without cleft palate (CLP), or cleft palate alone (CP) are the most frequent cranio-facial malformations in humans. The prevalence in France is 1/700 births, but incidence varies according to geographical origins from 1/300 births for Asians to 1/2500 births among Africans [1-3]. Two clinical forms are generally distinguished: CP, and unilateral or bilateral CLP which account for 70 to 80% of cases.

The diagnosis of these malformations may be delivered either *in utero* from prenatal scans, or at birth. The consequences of CLP are both aesthetic and functional (phonation, hearing, swallowing, chewing and ventilation are affected); there are also psychological consequences (construction of a self-image, relational disturbances). Over the years, numerous studies have been performed on the psychological effects of CLP, both for the child and for the parents. One review of the literature [4] notes that these studies overall do not conclude to any major psychosocial problem. Individuals presenting a CLP do not appear to be clearly affected by psychological, and even less psychiatric, problems. However disturbances have been described: behavioural disturbances, anxiety, depression, aesthetic dissatisfaction with facial appearance, these being observed in both children and adults. The difficulty in interpreting these signs resides in the many factors liable to influence this type of condition (family environment, the size and type of the cleft, the surgical protocol, growth, the social environment etc. [5].

Careful attention to what families have to say in the course of the numerous appointments required for treatment brings to light the importance, for the development of the child affected, of the trauma experienced by parents when the malformation is discovered - often seriously affecting the facial appearance of the baby. It also focuses the importance of the psychological context within which the parent–child relationship becomes established. The early relationship of parents with their newborn child is based on conscious and unconscious emotions which for the most part are relayed by touch, tone of voice, looks, and facial expressions. When an infant has a CLP, the parents are unexpectedly confronted with a damaged, split-open face, and the emotional overload of an event of this sort can hinder their affective investment. Looking at their newborn child's deformed face obviously generates contradictory emotions: distress, horror, guilt, desire to mend or to protect and so forth [6]. The malformation can prevent recognition of an intergenerational affiliation, and hamper the integration of the child into the family [7]. Thus the parent–child relationship can be affected from birth.

### The surgical treatment of CLP

The care provision for children with CLP requires several surgical interventions depending on the seriousness of the malformation. The first intervention is on the lip, and a second, a few months later, is on the palate. The way in which the corrections are performed depends on the defect and the protocol chosen by the surgical team. To date, no generic protocol has been recognised by the medical community as a whole. Each patient is cared for according to the experience and specific choices of the team in charge. In Europe there are more than 210 referral centres for children with CLP, and some 190 different protocols. These disparities can be explained by the fact that the aesthetic and functional result of a protocol can only really be evaluated in adulthood, when the child's growth is complete. Yet the period between the diagnosis and the instatement of the protocol by way of the first surgical procedure is crucial, since it is in that period that the relationship between the newborn child and the parents becomes established. The malformation, particularly in the case of cleft lip which directly affects the child's face, is likely to affect the parents' attachment to the child.

In France, as elsewhere, the planning of the surgical intervention varies according to the care facility. Certain teams are in favour of early intervention, immediately after birth, so as to establish proper functioning (ventilation, swallowing and phonation) as soon as possible, and also to reduce the psychological impact of the defect on the parents and the family circle. Other teams prefer to wait three of even six months. By thus delaying the intervention, these teams aim to make use of the particularly fast growth during this period. The individualisation of the different muscles is thus easier, and this enhances the precision and the quality of the surgical gesture. For certain authors, these differences in timing could condition the child's cognitive development, ultimately influencing achievement in school [8,9]. These authors suggest that the disfigured faces of these children are less attractive, and also that it is difficult for parents to interpret their children's facial expressions. This is important in the first months of life. Murray et al in 2008 [10] showed interdependence between a child's cognitive development and the timing of the surgical intervention. Development appeared to be retarded in case of difficulties in relations between mother and child at the age of two months, and if the first intervention was planned at a later stage. In contrast, no difference with the control group was noted for the subgroup of children in this study for whom surgery was planned early. A disfigured child can affect the mother psychologically, and upset the relationship. In this case the length of time during which the child remains disfigured could explain the cognitive delay.

### The importance of informing, and instatement of care

All the studies on the early life of children with CLP underline the importance of the quality of information right at the start of the relationship with the care team, and at the time of the disclosure of the diagnosis. In 2004 Rey-Bellet and Hohlfeld [11] showed that a larger proportion of families deplored the lack of knowledge, know- how and tact among healthcare teams when the childbirth occurred in a peripheral maternity hospital rather than a large central hospital. When the diagnosis was prenatal, the awareness of the meaning of the malformation is acquired in stages [12,13]. When the diagnosis occurs at birth, the awareness is immediate because the defect is visible, but this does not mean that acceptation is immediate [14,15]. From the outset, it is important to help parents "invest in" this child who is "different" from the child they expected and hoped for; they should be helped, too, to become care auxiliaries for their infants, by way of attentive listening and information from the teams supporting them [11].

## Methods/Design

### Main hypothesis

The main hypothesis of this research is that the longer the time lapse before the first surgical intervention, the more likely are parental perceptions and feelings to upset the parent–child relationship and affect the harmonious development of the child.

### Secondary hypothesis

There are also two secondary hypotheses:

1) that the parents for whom it has been possible to give a prenatal diagnosis are better prepared to accept the waiting time

2) that with time, the negative feelings of parents in the later surgery group (3 to 6 months after birth) tend to decrease and to come into line with those of parents whose children have had an early intervention, and also that the child's distress tends to decrease.

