### Experimental chronology

According to the type of CLP and the healthcare facility involved, the time lapse between diagnosis and the first surgery varies from birth to six months. Two evaluation times are planned:

· T0, when the infant is 4 months

· T1, when the child is 12 months, i.e. 6 months or more after the first surgical intervention

The choice of positioning T0 at 4 months is based on the following arguments:

· Because of the variability of the protocols used by the surgical teams in each of the centres, it is not possible to define T0 and T1 that correspond to a specific examination for all the centres;

· At this age, the children for whom the surgery occurs early have already had their operation. They can therefore be compared to children whose operation is to occur subsequently (up to 6 months), the two groups comprising roughly equivalent numbers. In a more detailed analysis, it will be possible to compare the children receiving surgery at birth with those receiving surgery at three months or more.

The choice of positioning T1 at 12 months is justified by the following argument:

· When the child is one year old, this is sufficiently distant from both birth and the first surgical intervention (by at least six months) to enable a repeat of examinations and questionnaires used in the first stage of the study. This will enable comparison of psychological perceptions of the parents and the relational development of the child between T0 and T1, as well as exploration of the question of the timing of surgery.

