## Statistics

### Description of the statistical methods to be used

The ADBB score measured at 12 months is used as the main criterion to compare children receiving early intervention with those receiveing a later intervention. Likewise, for the parents, the PSI scores are compared between the early and later intervention groups.

A descriptive analysis of the variables will be performed. The mean, median, standard deviation and range will be provided for continuous variables, as well as proportions for categorical variables, along with 95% confidence intervals.

Scores for infant withdrawal and parental stress (ADBB and PSI in particular) will be analysed in relation to the time-lapse (two groups) before surgery (Wilcoxon-Mann- Whitney non-parametric test).

The correlations between ADBB scores and the different measures among parents (in particular PSI scores) will be studied using the Spearman correlation coefficient.

A multivariate analysis (multiple regression after transformation, where needed, of the dependent variable) will be performed to take into account the variables affecting the scores.

For all the analyses, an adjustment will be performed to take into account the type of cleft (labial cleft alone, or labial cleft with cleft palate) and whether it is unilateral or bilateral.

The analyses will be performed with SAS statistical software, release 9.2., SAS Institute Inc., Cary, NC, USA).

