**Priority n°4**: The effects of the moment at which the diagnosis is received - before or after birth.Few studies have explored this theme. Better understanding of the factors liable to influence the perception of the diagnosis is required (parental stress, family support, the importance of the choice of neonatal care procedures). It is likewise important to know the manner in which parents were informed, and whether or not psychological back-up was offered. One of the secondary hypotheses of the present study is that the parents for whom a prenatal diagnosis was possible are better prepared to tolerate the waiting period until surgery.

**Priority n°5**: Care and treatment protocols for CLP.It is important to analyse the care strategies implemented for children with CLP, and also the chronology and frequencies so as to gain a better understanding of possible long-term consequences. The medical files stored in each of the participating centres give an account of the history and the chronology of the medical acts performed. Thus the protocols can be compared, in particular between the two Reference Centres in France (Lille and Paris) and the two Competence Centres (Nancy and Strasbourg).

Finally, and above all, if the results of the study point to the need for psychological support for parents of children with CLP, regardless of the timing of surgery, a list of correspondents could be made available by a reference psychiatrist belonging to the healthcare team (a recommendation of the Cleft Palate Cranio-facial Association quoted by Collet and Spetz in 2007) [29].

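### The prenatal-diagnosis hypothesis concerns tolerating the wait for surgery, but the only diagnosis comparison stated pools all families at 12 months, when none is still waiting

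*Protocol article*

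**What the plan says.** The article's section on secondary hypotheses puts forward that "the parents for whom it has been possible to give a prenatal diagnosis are better prepared to accept the waiting time". The section on secondary objectives repeats the idea: parents for whom "a prenatal diagnosis was possible are better prepared to tolerate the waiting period until surgery". Both wordings concern families who have a wait to get through.

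The abstract (Methods/Design) takes the ADBB and PSI scores at one year as the main criteria. They serve to compare early with late surgery and, as a separate contrast, "those where the diagnosis was obtained prior to birth with those receiving it at birth". The inclusion criteria form the two diagnosis subgroups over all included children.

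The statistics section says the scores "will be analysed in relation to the time-lapse (two groups) before surgery". It adds that "an adjustment will be performed to take into account the type of cleft" and whether it is unilateral or bilateral, and that a multiple regression "will be performed to take into account the variables affecting the scores". It names neither time of diagnosis nor an interaction.

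The experimental chronology places T1 at 12 months, at least six months after the first operation. At T0 (4 months) the early group has already been operated on; of these children it says "They can therefore be compared to children whose operation is to occur subsequently (up to 6 months", the two groups being of roughly equal size.

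**The concern.** A hypothesis about tolerating the wait is a claim about the diagnosis effect in families who wait, or about how that effect changes with the length of the wait. The stated contrast differs from this in two ways.

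- **Population.** It mixes families operated on immediately after birth (the Lille protocol) with families who waited three to six months.
- **Time.** It is read when no family is waiting any longer. T0, when part of the cohort still is, is not used for it.

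A pooled difference could therefore appear although prenatal diagnosis does nothing for the wait, for instance because it helps all parents alike. It could also be small although prenatal diagnosis helps precisely those who wait. Either result could be misread as an answer to secondary hypothesis 1.

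**Working it through.** **1. The plan's own figure.** Inputs from the sample-size section: ADBB difference 2, SD 3.78, two-sided 5%, power 90%.

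n per group = 2 × [3.78 × (1.960 + 1.282) / 2]² ≈ 75.1, or 76 rounded up. With 75 per group the power is 0.900. The stated 75 per group, 150 in all, reproduces. It is sized for early versus later surgery only.

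**2. Assumptions.** The article does not give the share diagnosed prenatally (f) or the share who really waited (w). I take f = 50% (range 30–50%) and w = 50% (range 25–75%). The central w fits the roughly equal split at 4 months. The true benefit is set to exist in waiters only. Power is Φ(effect/SE − 1.96).

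**3. Benefit of 0.5 SD in waiters, N = 150, f = w = 50%.**

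- Pooled contrast, 75 v 75: effect 0.5 × 0.5 = 0.25 SD; SE = √(2/75) = 0.163; ratio 1.53; power 33%.
- Within waiters, 37.5 v 37.5: effect 0.5 SD; SE = √(2/37.5) = 0.231; ratio 2.17; power 58%.
- Interaction, four cells of 37.5: effect 0.5 SD; SE = √(4/37.5) = 0.327; ratio 1.53; power 33%.

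**4. The same on the ADBB scale: 2 units (SD 3.78) in waiters only.**

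| f | w | Expected pooled difference | Pooled power | Within waiters | Interaction |
|---|---|---|---|---|---|
| 50% | 25% | 0.5 | 12.5% | 36.7% | 28.9% |
| 50% | 50% | 1.0 | 36.7% | 63.0% | 36.7% |
| 50% | 75% | 1.5 | 68.1% | 80.1% | 28.9% |
| 30% | 25% | 0.5 | 11.2% | 31.7% | 25.0% |
| 30% | 50% | 1.0 | 31.7% | 55.6% | 31.7% |
| 30% | 75% | 1.5 | 60.5% | 73.0% | 25.0% |

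**5. What does not depend on the assumed shares.** With the same diagnosis mix in both timing groups, the pooled effect is w times the effect in waiters. The pooled test ratio is √w times the within-waiters ratio (check: 2.165 × √0.5 = 1.53). For any w below 1 the pooled contrast is diluted and has less power than the within-waiters contrast.

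**6. What 150 children can show on the interaction.** In a balanced 2×2, the ADBB interaction detectable with 90% power is 3.242 × 3.78 × √(4/37.5) ≈ 4.0 units. Detecting 2 units would take 16 × (3.78 × 3.242/2)² ≈ 601 children.

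**The case against.** The strongest reply is that the plan is unspecific rather than committed to the wrong test. The pooled contrast is part of one sentence in the abstract and is not tied to secondary hypothesis 1. The abstract's background speaks of comparing results while "also distinguishing the subgroups of parents who were given the diagnosis" before birth, which could mean the timing comparison broken down by diagnosis. The terms of the regression are left open. This stands to the extent that a matching analysis is not excluded. But none is stated, and the one diagnosis comparison that is stated does not match the hypothesis. Nor does the article say that a pooled difference will be reported as evidence on tolerating the wait; that is a risk of misreading, not a stated intention.

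A reader might infer that half the children hardly waited. The documents do not support this. Only Lille operates at birth, and its share is not given. The early half at 4 months also takes in Strasbourg, which defers surgery by 3 months.

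A reader might also infer that the matching test simply has more power. That is true of the within-waiters contrast, but a general benefit of prenatal diagnosis would make that contrast positive too. The interaction separates the wait from a general benefit, and at an even split it has the same power as the pooled test.

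Finally, the article sometimes counts the wait from diagnosis rather than from birth. On that reading prenatally diagnosed families wait even where surgery is immediate. This is a reason to define the wait. It does not rescue a pooled contrast read after every operation.

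**Conclusion.** The point holds as a mismatch between a stated hypothesis and the only stated comparison that bears on it. The mismatch itself needs no assumed figure. Its size does: with half of families waiting, a benefit confined to them is halved in the pooled contrast, and over 25–75% waiting a true 2 ADBB units becomes 0.5 to 1.5.

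The case for the change is that it estimates the right quantity, not that it brings adequate power. At 0.5 SD in waiters, with half diagnosed prenatally and half waiting, the interaction has about 33% power and the T0 contrast 58%. The T0 figure also assumes about 75 children not yet operated on at 4 months. Surgical timing follows the centre, so the interaction is also partly a comparison between centres, a further reason to call it exploratory.

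This is a secondary hypothesis. The change is worth making, but the main timing comparison is unaffected.

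**What to change.** Add to the statistics section that secondary hypothesis 1 is addressed by:

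- (a) a term for time of diagnosis by time to surgery in the multiple regression already planned, as the estimate specific to the wait;
- (b) as support, prenatal versus at-birth diagnosis at T0 among children not yet operated on.

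Report each with its 95% CI and label both exploratory, because the 150 children were sized only for early versus later surgery.

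Define later surgery once. The secondary hypotheses use 3 to 6 months after birth, while the chronology splits at 4 months, so a 3-month operation falls on different sides. State also whether the wait runs from birth or from diagnosis.

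Keep the pooled one-year comparison, described as the general effect of prenatal diagnosis and not as evidence on tolerating the wait.

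The cost is a few sentences. The surgeon's information sheet already records time of diagnosis, and surgical timing and T0 scores are collected. No visit or child is added.

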### Main evaluation criteria

The main criteria used in this research to assess the psychological state of the infants and parental stress, as well as any possible parental psychopathology, are provided by the following measures:

1) for the children, the Alarme Détresse BéBé (ADBB) scale which measures relational withdrawal in infants. The measure is applied by a specially trained mental health professional [16]

2) the Parenting Stress Index (PSI) which enables screening for parental attitudes that could be risk factors for the development of emotional and developmental disturbances in a young child [17].

### Secondary evaluation criteria

The secondary evaluation criteria are provided by the other questionnaires selected for this research, which are:

1) the Indice de Détresse Psychologique - Enquête Santé Québec health survey (IDPESQ) [18] and the Edinburgh Post-partum Depression Scale (EPDS) [19,20] which measure the psychological state of each parent

2) the Impact On Family Scale (IOFS) [21] which assesses the family, social and financial impact of the malformation

3) Spanier's Dyadic Adjustment scale in the short version, which explores the parental couple [22,23]

4) specifically developed questionnaires collecting information on the perception of the malformation and the care team, and on the parents' present relationship with their child. These questionnaires were designed to adapt to the moment of diagnosis (antenatal or at birth).

